#### Resting state brain activity

Resting state (rs)-fMRI identifies baseline brain activity of spontaneous blood-oxygen-level dependent (BOLD) fMRI signals and its analysis reveals changes in organization of large-scale functional networks, including oxytocinergic and related networks. Participants will be instructed to lie in the scanner with their eyes open and to try focusing on the presented fixation cross.

#### Structural brain markers

The structural measurements in this clinical trial will serve the comparison between ASD patients and HCs, not the comparison of the treatment groups (OXT vs. PLC).

##### Diffusion tensor imaging (DTI)

One DTI measurement will be acquired from each participant. Participants will be asked to lie particularly still during this measurement.

##### T1-weighted image

A three dimensional T1-weighted MR image will be obtained from all participants. All images will be examined and approved for inclusion by the study doctor at the respective institute.

### Primary outcome

Neural correlates of socio-affective and -cognitive tasks in ASD patients and HCs will be assessed after PLC and after OXT administration at two time points (cross-over design) using fMRI. For this study the primary outcome measure will be the neural network activity that is associated with the different social paradigms.

### Secondary outcomes measures and potential outcome mediators

Secondary outcomes entail behavioral measures that are collected during the fMRI sessions, including response times and ratings. Further, physiological measures that indicate affective arousal related to dACC and AI activity such as pupil dilation [see [47] for further details] heart rate and skin conductance responses are collected in the fMRI and fixation patterns and respiratory frequency will be recorded.

In addition to the secondary outcome variables, multidimensional aspects of autism and participants personality traits will be assessed with a questionnaire test battery, including: basic sociodemographic questionnaire, basic diagnosis and medication questionnaire (for patients only), number-symbol-test, digit-repetition test (part of the Hamburg-Wechsler-Intelligenztest für Erwachsene (HAWIE, since 2012 WAIS-IV)), brief symptom inventory (BSI-53) [48], WHO Disability Assessment Schedule [49], childhood trauma screener [50], clinical global impression scale (for patients only) [51], Trail Making Test A and B [52], vocabulary knowledge test (WST) [53], behavioral inhibitory scale (BIS) and behavioral approach scale (BAS) [54], Barratt impulsiveness scale [55], positive and negative affect schedule, interpersonal reactivity index (IRI) [56], Toronto alexithymia scale (TAS-20) [57], social interaction anxiety scale (SIAS) [58], Beck depression inventory (BDI-2) [59, 60], autism quotient (AQ) [37] state-trait-anxiety index – state (STAI-S) and state-trait-anxiety index – trait (STAI-T) [61], and an intelligence quotient (IQ) – test will be done. All data information will be entered in a database and are intended to be used for statistical analyses.

### Statistical analysis

#### Behavioral analyses plan

Raw data of all key variables will be tested for normality prior to analysis. Appropriate transformations (or non-parametric tests) will be conducted accordingly. Analyses will be done using repeated-measures analysis of variance (AN(C)OVA) and mixed models as primary designs. Difference scores will be calculated on every dependent variable for participant (ASD vs. HC) and treatment (OXT vs. PLC) groups. All measures will be compared between participant (ASD vs. HC) and treatment (OXT vs. PLC) groups and interaction effects (group x treatment) will be explored. Trait questionnaires may additionally be used as regressors when they can potentially explain behavioral differences between participant or treatment groups. After the T1 and the T2 visit, participants will be asked to guess whether they have received OXT or PLC. This information allows us to calculate a chi square test after unblinding, to check whether participants knew or did not know which nasal spray they received.

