### Trial design

This clinical trial is a multi-centered, two-arm, randomized, double blind placebo-controlled study with a cross-over design. Three visits and two functional magnetic resonance imaging (fMRI) assessments will take place for the participants of both groups (ASD and HC). The first visit includes a medical interview and an explanation of the informed consent; this visit determines whether the participant can be included in the study (T0). Once the participant is eligible to participate, he will be randomized to arm A or arm B, which determines whether he receives OXT or placebo (PLC) at the next visit. During the next visit (T1) the OXT or PLC administration and the first fMRI assessment will take place. The next visit (T2) will include the same measurements as T1 and will be scheduled approximately two weeks after T1, to ensure no carry-over effects if OXT had been administered at T1. After completion of T1 and T2 each participant (HCs and ASD patients) will guess which nasal spray they have received (Fig. 1).

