### Sample size

The sample size is calculated for the two primary outcomes: 1) the effects of the OXT treatment on the neural system functioning in the ASD population and 2) the comparison between the ASD and the HC group in the placebo condition. The first comparison for the power calculation is the cross-over comparison of the OXT effects on neural network activity in the ASD patient group, because the recruitment plan is determined by the ASD patient group. Meta-analytic estimates of intranasal OXT effects on the behavior of ASD patients indicated a medium effect size of approximately *d* = 0.60. We expect neural OXT effects to be bigger than behavioral OXT effects, because OXT has a stronger penetrance on the brain. Therefore, we adjusted the effect size for OXT’s influence on brain activity to *d* = 0.65. For all power calculations, a power of 80 % and a significance level of alpha = 0.001 was chosen and the analyses were carried out with PASS12. To obtain sufficient power for two-tailed t-test analyses in a cross-over design, *N* = 88 ASD patients need to be included in the analyses. Based on our prior experiences with ASD patients in behavioral and fMRI studies [3, 38] and the relatively short duration of the current study led to a drop-out estimation of 13 %. To allow for this drop-out, we need to initially recruit *N* = 102 patients. Due to the one on one matching it is necessary to include as many HCs as patients (*N* = 88). Recruitment for HCs will thus continue until each ASD patient has a proper match.

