#### T-1 weighted image analysis

A structural MPRAGE t1-weighted image will be analyzed and preprocessed with SPM. It will mainly be used as a reference image for the functional paradigms. Furthermore, the potential differences between groups will be analyzed.

All secondary outcome measures will be analyzed analogously.

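### The normality check is made on raw behavioral data, but the within-person oxytocin–placebo contrasts depend on residuals and differences; the cost is modest and confined to secondary outcomes

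*Protocol article*

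**What the plan says.** The rule is in the protocol article under Behavioral analyses plan: "Raw data of all key variables will be tested for normality prior to analysis". The next sentence gives the consequence: "Appropriate transformations (or non-parametric tests) will be conducted accordingly". The section then names the models: "Analyses will be done using repeated-measures analysis of variance (AN(C)OVA) and mixed models as primary designs". It adds: "Difference scores will be calculated on every dependent variable for participant (ASD vs. HC) and treatment (OXT vs. PLC) groups". It plans comparisons by participant group, by treatment, and for their interaction. The normality check is tied neither to the difference scores nor to the residuals of the models.

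Trial design describes a "two-arm, randomized, double blind placebo-controlled study with a cross-over design", so each patient's OXT value is compared with his own PLC value.

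The outcomes concerned are described under Secondary outcomes measures: "Secondary outcomes entail behavioral measures that are collected during the fMRI sessions, including response times and ratings". A later sentence, "All secondary outcome measures will be analyzed analogously", may extend the rule, but it stands at the end of T-1 weighted image analysis and it is not clear which plan it refers to. The section on task-related fMRI, which covers the primary outcome, contains no such rule.

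**The concern.** Repeated-measures ANOVA and mixed models rest on the distribution of within-person errors when they estimate a within-person contrast. A paired comparison rests on the OXT–PLC differences. Raw values also carry the stable differences between people, which the paired comparison removes. If those differences are skewed, raw data can fail a normality test while the model's errors are well behaved, and the rule then sends the analyst to another scale or another test for no good reason.

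Two things are at stake. One is power, by an amount that depends on which non-parametric test is chosen; the article names none. The other is interpretation. An interaction between group and treatment on the raw scale is a different quantity from one on a log scale, and the rule lets the data choose between them.

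**Working it through.** **Inputs from the article (Sample size).** 88 patients analyzed, d = 0.65, two-tailed alpha 0.001, power 80%, drop-out 13%.

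**The plan's own figure.** For a 2×2 cross-over t-test with d in units of the within-person SD, the non-centrality is d·√(N/2) = 0.65·√44 = 4.31 on N − 2 = 86 degrees of freedom. Power is 0.812, and 88 is the smallest even N that reaches 80%. Allowing for drop-out, 88/(1 − 0.13) = 101.1, so 102. Both figures reproduce.

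**Model for the check.** Value = person level + treatment effect + normal error. The shape and spread of the person levels, the period effect and the use of Shapiro-Wilk at 5% are assumptions; the article gives none of them.

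**Step 1: how often does each check reject, with exactly normal errors and n = 88?** With within-person SD 1 and between-person SD 1.5 (intraclass correlation, ICC, 2.25/3.25 = 0.69) and mildly to strongly skewed person levels, raw values fail in about 45–84% of trials and differences in 4–5%. A wider grid, testing the raw values of one visit:

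| Person levels | ICC 0.3 | 0.5 | 0.7 | 0.85 |
|---|---|---|---|---|
| Normal | 5% | 6% | 4% | 4% |
| Gamma, shape 4 | 9% | 23% | 44% | 70% |
| Lognormal | 23% | 49% | 79% | 96% |
| Exponential | 20% | 52% | 86% | 98% |

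Testing the differences rejects in about 4–6% in every cell. Pooling the ASD and healthy-control groups adds little unless they lie far apart: with normal person levels, separations of 1, 2 and 3 between-person SDs give 5%, 8% and 65%.

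**Step 2: what does leaving the planned test cost?** Exponential person levels, ICC 0.7, effect in within-person SDs:

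| Setting | Cross-over t with period | Paired t, no period | Signed-rank | Unpaired rank test |
|---|---|---|---|---|
| Effect 0.65, alpha 0.001 | 81% | 81% | 78% | 15% |
| Effect 0.42, alpha 0.05 | 77% | 77% | 75% | 34% |
| Effect 0.42, alpha 0.05, period effect 1 SD | 79% | 64% | 60% | 30% |
| No effect, alpha 0.05 | 5% | 5% | 5% | 0.2% |

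Across the skewed settings at alpha 0.001 the signed-rank loss is about 3–5 points; at alpha 0.05 it is about 2. In the third row, 79 − 64 = 15 of the 79 − 60 = 19 points come from leaving out the period, not from ranking. A rank-sum test of period differences between the two sequences keeps 77%, against 80% for the cross-over t-test in the same simulation.

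**Step 3: what does a change of scale do to the interaction?** Assume a 40 ms reduction in both groups, from baselines of 600 and 800 ms. The raw-scale interaction is zero. On the log scale the effects are ln(560/600) = −0.069 and ln(760/800) = −0.051, which differ by 0.018. With 88 per group and alpha 0.05, the raw-scale test rejects in about 5% of runs. The log-scale test rejects in 27%, 15% and 11% at within-person SDs of 40, 60 and 80 ms.

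**The case against.** **Raw spread matters for part of the plan.** This stands. In the one-visit comparison of ASD with healthy controls, the residual is the raw value minus its group mean, so between-person skew is part of the error. With exponential person levels (SD 1.5), within-person SD 1, 88 per group, a shift of 0.7 and alpha 0.05, the rank-sum test has 81–82% power and the t-test 73%. Reacting to skew helps there, so it would be wrong to say that raw distributions never matter.

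**Rank methods can handle the design.** This also stands. A rank-sum test of the OXT–PLC differences between groups tests the interaction (78% power against 81% for the t-test, with 5% type I error), and a rank-sum test between sequences handles the period. A reader might infer that a non-parametric fallback must lose the interaction or the visit effect. It need not, and the article already plans difference scores.

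**The worst power figures need a test the plan never proposes.** The 15% and 34% belong to an unpaired rank test on paired data. The article does not exclude that test, but nothing in it points to it. Also, the sample-size effect, "influence on brain activity to *d* = 0.65", concerns the brain, not behavior; it serves here only as a convenient size.

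**A transformation may be right.** If response-time errors are multiplicative (assumed), a log scale gains power: 74% against 69%. That is a reason to choose the scale in advance, not to let a raw-data test choose it.

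**Detail may be in the full protocol or analysis plan.** The choice of normality test or rank test may well be. But the article does state what is to be tested, and a fuller document that followed it would inherit the problem.

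**Conclusion.** The point holds in limited form. The rule directs the check at the wrong quantity for the within-person contrast and for the group by treatment interaction. With skewed person levels it would often move the analysis away from a valid model: about 45–84% of trials in the main setting, 9–98% over the wider grid. With normal person levels there is no excess. Everything above the nominal rate therefore rests on the assumed skew and ICC.

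The cost is modest: about 3–5 points of power with a paired rank fallback, more only if pairing is ignored or a sizeable period effect is left out, and an interaction whose meaning depends on a scale chosen after seeing the data.

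Three stronger readings are not supported:

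- A reader might infer an inflated error rate. No test of the treatment effect exceeded about 5% under the null. The 11–27% log-scale rejections detect a difference that is real on that scale; they are not false positives.
- A reader might infer that the primary result or the sample size is at risk. The fMRI analysis does not use this rule, and 88 and 102 reproduce.
- A reader might infer that every secondary outcome is covered. The rule is written for key variables in the behavioral plan, and the reach of the sentence under T1-weighted imaging is uncertain.

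**What to change.** Replace the raw-data test with these provisions:

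1. Set the analysis scale of each key behavioral variable in advance, for example a log scale for response times if judged appropriate.
2. Fit the planned mixed model as the main analysis. Then inspect its residuals and, for within-person contrasts, the OXT–PLC differences. For the one-visit ASD versus control comparison, inspect residuals around the group means.
3. If these depart markedly from normal, keep the model and report bootstrap or robust confidence intervals.
4. Report rank tests on the differences as sensitivity analyses: signed-rank within patients, rank-sum between groups for the interaction, and rank-sum between sequences where a period effect is allowed for.
5. State which outcomes the rule covers, so that the sentence under T1-weighted imaging is no longer ambiguous.

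The cost is a few sentences in the analysis plan and slightly more analysis work. It needs no extra patients or data.

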#### Task-related functional MRI analysis

All fMRI data will be preprocessed with SPM and afterwards statistical analysis will be carried out using the general linear model [62]. For all experiments, onset and duration of the block or event will be modeled. The respective regressors will be convolved with a canonical hemodynamic response function (HRF) and head motion will be accounted for by modeling the six motion parameters for each subject. If the head movement exceeds the usual tolerance of 3 mm, additional movement corrections will be carried out. Differences between participant (ASD vs. HC) and treatment (OXT vs. PLC) groups and interactions between participant and treatment groups on BOLD signal changes will be evaluated for each task (ANOVA and/ or t-tests). Whole brain and paradigm-specific region of interest (ROI) analysis, based on information from previous studies assessing these paradigms and meta-analyses of the investigated functions will be done. For the *emotional matching task*, two main effects (sociality and emotional valence) as well as the interaction effect (sociality x emotional valence) will be calculated. In the *social and monetary incentive delay task* two main effects (task and phase) will be calculated as well as the interaction effect (task x phase). The *EmpaToM* will include main effect contrasts of empathy and ToM. For this paradigm we may for example use the AI and the dACC as ROIs, because these regions have consistently been identified with empathy [45, 46]. Furthermore valence and compassion responses might be added as parametric modulators to further explain task-related brain activation. All task-related main effects and interactions will be calculated for participant (ASD vs. HC) and treatment (OXT vs. PLC) groups. Personality trait scores may also be added as regressors in the fMRI analysis to investigate secondary research questions and explain specific variance. All interaction effects will be followed up and more detailed investigations will be carried out. Additionally, we will extract the peak BOLD-fMRI activation levels from ROIs that have previously been reported in these paradigms or meta-analyses, and import the extracted values into SPSS or R for additional statistical calculations. Furthermore, we plan to perform connectivity analyses with paradigm-specific peak regions. The results of each fMRI paradigm will be analyzed and published separately, before the results of multiple paradigms will be combined to generate an overarching picture of OXT’s effects on social cognition/social functioning.

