### Randomization

After completion of baseline assessment, ASD patients will be assigned to either arm A (T1: OXT, T2: PLC) or arm B (T1: PLC, T2: OXT). The order will be determined with a block randomization of 2 or 4 participants per block for arm A and arm B. The order of the three different experimental paradigms is also randomized with a fixed block size of six (123/132/213/231/312/321) so that each combination of assessment order is possible to ensure equivalent OXT levels for all paradigms. Thus, a second randomization list for the different paradigms, one for arm A and one for arm B, will ensure that each order of the experimental paradigms will be equally distributed in both arms.

The randomization lists will be independently generated for both sites (Leipzig/ Lübeck) to guarantee balancing for both sites. Thus, there will be three lists for each site, one arm-randomization list and two paradigm randomization lists. The lists are solely generated for the ASD population; HCs will be matched to the patients. The matching is also done by each center separately. Every matched participant will receive the same experimental order as the corresponding ASD patient.

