### MRI assessment battery

#### Emotional matching

The emotional matching task was selected as a well-established fMRI task investigating emotion processing. In order to further optimize the task, we adapted the original emotional matching paradigm [39] by choosing more comparable control stimuli. Participants are presented with a total of 60 faces (20 positive, 20 neutral, 20 negative), 60 social scenes (20 positive, 20 neutral, 20 negative) and 60 non-social scenes (20 positive, 20 neutral, 20 negative). This stimulus set results in 9 conditions: positive faces, neutral faces, negative faces, positive social scenes, neutral social scenes, negative social scenes, positive non-social scenes, neutral non-social scenes and negative non-social scenes. Each presented picture consists of three single pictures arranged in a pyramidal disposal, in which the picture on the top is identical to one of the pictures below. Participants need to decide by button press whether the left or the right picture matches the one on top. Each stimulus picture will be presented for 4 s and 4 pictures of the same category (e.g. positive social scenes) constitute one block. The different category blocks will be presented in a randomized manner. This experiment consists of two parallel stimulus sets so that version A can be shown at one visit and version B can be shown at the other visit.

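### No visit (period) term is named for the oxytocin–placebo cross-over comparison, and no rule ties stimulus version to visit; the main cost is power, and the repair is cheap

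*Protocol article*

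**What the plan says.** All references are to the protocol article.

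- **Design.** Under Randomization, patients go to arm A (oxytocin at T1, placebo at T2) or arm B (the reverse), in blocks of 2 or 4, with separate lists for each site. Each healthy control follows the order of the matched patient. The lists are counted: "Thus, there will be three lists for each site, one arm-randomization list and two paradigm randomization lists". Stimulus version is on none of them.
- **Stimuli.** Under Emotional matching, "version A can be shown at one visit and version B can be shown at the other visit"; the EmpaToM section is worded alike. The incentive delay tasks have two sets, each shown at T1 or T2. No section says which version goes with which visit.
- **fMRI analysis.** Under Task-related functional MRI analysis, the group-level comparisons are "Differences between participant (ASD vs. HC) and treatment (OXT vs. PLC) groups and interactions between participant and treatment groups on BOLD signal changes", by ANOVA and/or t-tests. Task factors, motion parameters and optional trait scores are also named.
- **Behavioural analysis.** "All measures will be compared between participant (ASD vs. HC) and treatment (OXT vs. PLC) groups", with the interaction explored. The methods are repeated-measures AN(C)OVA and mixed models, with trait questionnaires as possible extra regressors.
- **Sample size.** The calculation is for "two-tailed t-test analyses in a cross-over design", where "a power of 80 % and a significance level of alpha = 0.001 was chosen". It takes d = 0.65 and needs 88 patients analysed and 102 recruited.

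Neither analysis section mentions visit.

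**The concern.** In a two-period cross-over, each patient's oxytocin–placebo difference contains the treatment effect and, with opposite sign in the two arms, the T2–T1 shift. Such a shift is plausible here because the same tasks are repeated in the scanner and the stimulus set changes between visits. The wash-out addresses carry-over; it does nothing about habituation, practice or a change of stimuli.

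Without a visit term, the shift spreads the differences apart and inflates their variance. If one sequence has more completers, part of the shift also stays in the mean difference. The planned power is only about one point above 80%, so there is little room to absorb this.

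Version adds to the same problem. Tied to visit, it is part of the visit effect. Counterbalanced, it adds variance unless it has a term of its own.

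**Working it through.** **Inputs.** From Sample size: N = 88 analysed, 102 recruited, 13% drop-out, d = 0.65, two-sided alpha 0.001, power 80%. The article does not say which SD standardises d. The size of the visit effect is not given; 0 to 1.0 within-subject SD is assumed.

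**Step 1: reproduce the plan's figure.** Take d as the treatment difference over the within-subject SD. The 2x2 cross-over t-test has non-centrality d√(N/2) and N − 2 degrees of freedom. At N = 88 this is 0.65 × √44 = 4.31, giving 81.2% power. The smallest N reaching 80% is 87, so 88 for equal sequences. Allowing for drop-out, 88/0.87 = 101.1, rounded up to 102. Both plan figures reproduce. Reading d on the SD of the paired differences would need only 46 patients, so the within-subject reading is used below. With N − 1 degrees of freedom the answer is also 87, so the sample size does not reveal whether a visit term was intended.

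**Step 2: what the omission does.** Set the within-subject SD to 1, so a paired difference has variance 2. Let τ be the oxytocin effect, π the T2–T1 effect and e = (nA − nB)/N. The expected difference is τ − π in arm A and τ + π in arm B. Pooled without a visit term:

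- mean difference = τ − eπ
- variance = 2 + π²(1 − e²)

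A sequence main effect is constant within a person and cancels from the difference.

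**Step 3: power at 44:44.** Here e = 0 and the approximate non-centrality is 0.65√88/√(2 + π²) = 6.098/√(2 + π²). The formula is slightly pessimistic because the arm split is fixed, so simulated power is also shown.

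| Visit effect π (within-subject SD) | SD of differences | Non-centrality | Power, formula | Power, simulated | Power with visit term |
|---|---|---|---|---|---|
| 0 | 1.414 | 4.31 | 81.2% | 81% | 81% |
| 0.2 | 1.428 | 4.27 | 80.1% | 80% | 81% |
| 0.3 | 1.446 | 4.22 | 78.7% | 79% | 81% |
| 0.5 | 1.500 | 4.07 | 74.1% | 75% | 81% |
| 1.0 | 1.732 | 3.52 | 54.8% | 55–56% | 81% |

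By the formula, keeping 80% power without the term would need 90, 97 or 127 patients at π = 0.3, 0.5 or 1.0.

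**Step 4: unequal completers.** If 14 of 102 patients (51 per arm) drop out at random, arm A keeps 41 to 47 of the 88 (95% range). At 47/41, e = 6/88 = 0.068, so about 7% of the visit effect enters the estimate. For π = 0.5 that is 0.034 SD, or 0.034/0.65 = 5% of the planned effect. Unadjusted power is then 68% or 82%, depending on which arm is larger; with a visit term it is 81% either way.

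**Step 5: type I error.** Simulated under no oxytocin effect without the visit term, it is about 0.0005 (44:44, π = 0.5), 0.0008 (48:40, π = 0.5) and 0.0003 (48:40, π = 1.0), against the nominal 0.001. The inflated variance more than offsets the small bias.

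**The case against.** The strongest reply is that this is a condensed article. It lists comparisons of interest, not a closed model, and nowhere says that visit is left out. Repeated-measures ANOVA and mixed models can hold a visit term. The standard 2x2 cross-over t-test, which the sample size section may mean, removes the visit effect by construction. A fuller protocol or analysis plan may name the term.

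That defeats any claim that the analysis models group and treatment only. It does not remove the point. The article goes as far as naming optional trait regressors, and its stated tests include ordinary t-tests, so a reader following this text would not arrive at a visit-adjusted comparison.

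The design safeguards also count. Small blocks within site keep the sequences close to equal, and controls share their match's order. Hence the bias is small.

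Three stronger readings are tempting, and the documents do not support them:

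- **Sequence differences contaminate the oxytocin effect.** They cancel within person (Step 2).
- **Drop-out could produce a serious imbalance and bias.** A 49/39 split or worse has a probability of about 0.8% under random drop-out.
- **Version assignment biases the treatment effect directly.** That needs an allocation associated with treatment, and nothing in the text suggests one. The wording is compatible with version A always at T1, which would be acceptable with a visit term. What stands is only that no rule is stated.

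**Conclusion.** The point holds in a limited form. The analysis text names no visit term for the oxytocin–placebo comparison, although order is randomised and stimuli change between visits. The harm is lost power: negligible for a visit effect of 0.2 within-subject SD, about 6 points at 0.5 and about 25 at 1.0 with balanced sequences. Bias is limited to about 7% of the visit effect at the edge of the range expected from random drop-out, and false positives do not increase.

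These sizes rest on reading d as standardised by the within-subject SD, which reproduces the plan's N, and on assumed visit effects. A reader might infer that a significant oxytocin effect from this trial could not be trusted; the type I error results do not support that. This is a cheap improvement, not an essential correction.

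**What to change.** 1. Name visit (period) as a fixed effect in the oxytocin comparison for fMRI and behavioural outcomes, using either the 2x2 cross-over t-test or a mixed model with participant as a random effect.
2. In SPM, enter arm coded +1/−1 as a covariate on the oxytocin–placebo difference images, without mean-centring. The intercept is then the plain average of the two sequence means, which is free of the visit effect even when completers are unequal. Mean-centring would return the unadjusted mean.
3. State one version rule for each task. Either tie version to visit for everyone, so that the visit term absorbs it, or balance version within arm and give it its own term. This must be settled before scanning, because analysis cannot repair the allocation afterwards.

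The cost is one degree of freedom, one more if version has its own term, and a few sentences of text. N stays at 88 analysed and 102 recruited.
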